##### Humans

Case Report Forms (CRF) CRFs will be kept for each subject, for each data collection, i.e.

human survey and human fecal examination. Subjects will be identified by their administrative

village, natural village, house identification, and an individual identification within the house. In

addition they will be assigned a unique serial number which will be constant over time, and

enable longitudinal analysis. CRFs will be completed according to standard operation procedures

(SOPs). That is, all data on the CRF will be legibly recorded in black ink, corrections may only

be made by striking through an incorrect entry with a single line and entering the correct

information adjacent to it. The correction will be initialed and dated by the investigator or a

designated, qualified individual.

A migration CRF will be used to record exit from the study, the date of exit, and the reason.

In-migrants will not be recruited to the study, however their entry to the village will be recorded along with the date of entry, and the reason. Furthermore, these in-migrants will be tested and treated on entry.

Note: Only those who enter the study site during the transmission season and stay longer than two weeks will be examined and treated. If from an endemic area or are having water contact, need to be examined and treated. If living in the village, need to be examined and treated. All will be recorded.

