**Statistical Considerations**

**7.1 Outcome Measures**

The outcome measures for this study include the prevalences, infection and reinfection rates, intensities of infection and incidences. The end-point for the trial will be human infection rates. The efficacy of buffalo treatment will be measured by the accumulated comparison of human infection rates across intervention and control villages, and will be reflected in the predicted percentage of human infection-years prevented by the intervention. Human infection rates will be assessed at the end of each year for 4 years.

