**7.2 Outcome Measure Formulae**

Prevalence = No. of egg positive cases

No. persons at risk × 100

For the prevalence per village, the number of persons at risk would equal the village population.

Incidence of infection : Since all positive cases are treated (and confirmed negative) at the end of

each year, the incidence rate of infection for a year is the number of infected persons in the cohort

found at the end of each year (having been present during the year), divided by the number of

persons in the cohort present during the period.

Year K Incidence density = No. of infections at end of year K _____ × 100

(K=2 to 5) No. of persons in cohort at end of years K and K-1

To take account of drop-outs, where additional information is available on the timing, we will be

able to refine this estimate by using a ‘person-time denominator’, which modifies his or her

exposure time by drop-out time: person-time = date of drop-out – date of start of period:

Incidence of newly-infected: This measure examines the rate of infection in those not infected at

the end of the previous period (year). It is the number of infected persons in the cohort found at

the end of each year (having been present during the year), divided by the number of persons in

the cohort present during the period, and negative at the end of the previous year.

Year K Newly-infected = No. of infections at end of year K__________ × 100

(K=2 to 5) No. of persons in cohort at end of

years K and K-1, and negative at end of year K-1

Rate of reinfection: This measure examines the rate of infection in those infected at the end of

the previous period (year). It is the number of infected persons in the cohort found at the end of

each year (having been present during the year), divided by the number of persons in the cohort

present during the period, and positive at the end of the previous year.

Year K Re-infected = No. of infections at end of year K × 100

(K=2 to 5) No. of persons in cohort at end of years K and K-1,

and positive at end of year K-1

Intensity of reinfection: The intensity of infection for new cases and the intensity of reinfection

will be determined by the number of eggs per gram of feces, which is measured using the Kato-Katz thick smear technique.

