**7.3 Statistical significance, Generalizability and Power**

In order for this study to yield results that are statistically significant and are able to be applied to a population (i.e. generalizable), there needs to be adequate power and a sample size providing an accurate representation of the affected community. It has been determined that for generalizability and statistical significance, a minimum of 4 village pairs is required, with a sample size of 300 per village, with a village population of approximately 1000.

The following table shows the power calculations based on the above minimum considerations. The

table also shows these powers with varying degrees of the bovine effect on the village and the

percentage of the bovines that are actually treated.

Assumptions

- Design effect is 1.5, in other words the actual sample size is reduced by a factor of 1.5 to give an effective sample size. This reduction is due to the extra similarity within clusters that means the observations cannot be treated as independent.
- Assume an attrition rate between years 1 and 2 of 20%.
- Assume that years 1 and 2 are independent for the cumulative power.
- Target (net) sample size is the number obtained in each village for testing (after excluding non-compliers).
- Use a significance level of 1% year 1 and 5% year 2.
- This study works on treating the whole village.
- Assume a village size of 1000.

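### The optional person-time refinement of incidence counts drop-outs' time at risk but cannot count their infections, so the refined rate is too low

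*Protocol*

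**What the plan says.** Protocol Section 7.2 counts infected cohort members "found at the end of each year (having been present during the year), divided by the number of" members present over the period. The displayed formula makes that denominator "No. of persons in cohort at end of years K and K-1", that is, those who stayed throughout.

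A refinement follows. It opens "To take account of drop-outs, where additional information is available on the timing, we will be" able to refine the estimate with a person-time denominator, which modifies each drop-out's "exposure time by drop-out time: person-time = date of drop-out" minus the date on which the period began. No change to the numerator is given.

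On measurement and exits:

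- Section 7.1: "Human infection rates will be assessed at the end of each year for 4 years". Section 3.1 (Stages 4 and 7) places this stool survey in October-November.
- Sections 3.1, 5.1 and 5.2: the only other scheduled cohort stool comes one month after treatment, to check cure.
- Section 6, records for humans: "A migration CRF will be used to record exit from the study, the date of exit, and the reason". Form 5 (out-migration) has no stool field, and Section 4.2 relies on relatives or neighbours to report departures. By contrast, in-migrants are to be tested when they arrive.
- Section 7.3, power assumptions: "Assume an attrition rate between years 1 and 2 of 20" per cent.

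**The concern.** A rate needs its events and its time at risk to come from the same people under the same observation. The base formula meets this condition: those counted below the line are those who can be found positive above it. The refinement breaks it. A person who leaves in mid-year may already be infected, but nobody looks, so that person brings time without any possibility of an event.

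The unit is doubtful too. The Regimen in the Schema places human treatment just after the transmission season and bovine treatment just before and just after it, and Section 3.1 puts the bovine rounds in May and November. Exposure therefore appears concentrated between those months, yet the formula counts calendar days equally. Someone leaving in April would add about five months that may carry little exposure.

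Human infection rate is the trial's end-point, and the Analysis Plan feeds the empirical data into the mathematical model to test its predictions. The level of incidence matters for that purpose, as well as the contrast between arms.

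**Working it through.** The protocol states no incidence or bias figure for this point, so there is none to reproduce.

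**Inputs**

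- N = 300 cohort members per village (Section 3.1, sentinel cohort).
- d, the fraction leaving with a recorded date: 20% as an illustration, borrowed from Section 7.3; 5% to 30% as a range.
- t, mean time of exit as a fraction of the year: not in the protocol; assumed 0.5, with range 0.25 to 0.75.
- p, annual infection risk: not in the protocol; 12.5% assumed, the middle of the 10-15% human prevalence in the village selection criteria (Section 4.1).

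**Formulae**

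- Cases found at year end: N(1-d)p
- Base denominator: N(1-d)
- Refined denominator: N[(1-d) + d·t]
- Refined rate / base rate = (1-d) / [(1-d) + d·t]

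The ratio is below 1 whenever d and t exceed 0, and does not depend on p.

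**One village, d = 0.20, t = 0.5**

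- Completers: 300 × 0.80 = 240. Cases: 240 × 0.125 = 30.
- Base: 30/240 = 12.5 per 100.
- Refined: 30/(240 + 60 × 0.5) = 30/270 = 11.1 per 100.
- Ratio: 0.80/0.90 = 0.889, or 11% too low.

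**Range**

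| d | t = 0.25 | t = 0.5 | t = 0.75 |
|---|---|---|---|
| 5% | 0.987 | 0.974 | 0.962 |
| 10% | 0.973 | 0.947 | 0.923 |
| 20% | 0.941 | 0.889 | 0.842 |
| 30% | 0.903 | 0.824 | 0.757 |

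**Simulation** (2,000,000 persons, constant hazard, uniform exit times, p = 12.5%, d = 20%): base 12.49 per 100, refined 11.11. If infection at exit were also measured and counted, the person-time rate is 12.51. The shortfall therefore comes from the unmatched numerator and not from person-time as such.

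**Between arms** (t = 0.5 in both). The observed ratio is the true ratio times the intervention factor divided by the control factor.

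- Equal loss, 20% and 20%: 0.889/0.889 = 1, so the ratio is unchanged.
- Control 10%, intervention 20% (assumed): 0.889/0.947 = 0.94 for a true ratio of 1.00.
- Reversed: 0.947/0.889 = 1.07.

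**Absolute difference with equal loss of 20%.** Take a true ratio of 1 - 0.60 × 0.70 = 0.58, the simple product of effect size and coverage in the first row of the power table. The base rates are 12.5 and 7.25 per 100, a difference of 5.25. The refined rates are 11.1 and 6.4, a difference of 5.25 × 0.889 = 4.67.

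**The case against.** The strongest reply is about scope. The refinement is something the team says it will be able to do when timing is known. It is not the defined incidence, and neither Section 7.1 nor the Analysis Plan names it as the end-point analysis. The newly-infected and reinfection formulae have no person-time clause. A reader might infer that the trial's end-point is biased as planned. The documents do not support that, because the base formula stands without the refinement. This part of the reply holds.

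The size can be challenged as well. A reader might take the 20% as a yearly rate of dated departures. Section 7.3 gives it only as a power assumption between years 1 and 2 and does not say what it consists of. Some of it may be residents who stay but give no stool (Form 2D has codes for refusal and sickness), who would have no exit date. The inclusion criteria in Section 4.2 also screen out people expecting to migrate. The 11% is thus an illustration.

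A reader might further infer that the refinement creates or hides a treatment effect. The protocol gives no loss by arm. Human treatment and testing are the same in both arms, and villages are matched and randomised within pairs. With equal loss and timing the ratio is unbiased, and a gap of 10% against 12% moves it only to 0.936/0.947 = 0.99. The percentage of infection-years prevented is a relative measure and behaves in the same way. With about four pairs, however, exact balance cannot be assumed.

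Two smaller points stand in part. The refinement ends on a colon with nothing after it, so an unchanged numerator is the natural reading but not an explicit statement. The season's dates are not given and the baseline form asks about spring water contact, so low exposure before May is an inference.

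None of this makes the formula correct. Applied as written, it lowers the rate.

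**Conclusion.** Wrong as written, in an optional calculation. The refinement lowers incidence relative to the base formula by the factor (1-d)/[(1-d) + d·t]. That is about 11% if 20% of the cohort were dated exits at mid-year on average, and 6% to 16% for mean exit at 0.25 to 0.75 of the year. Absolute rates and differences shrink even with balanced loss. The rate ratio moves only if loss or its timing differs between arms; the 0.94 for 10% against 20% is conditional on assumed losses and is not a forecast.

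The direction rests on two readings: that the numerator is unchanged, and that no exit stool is taken. Reading the shortfall as bias against the true incidence also assumes that leavers and stayers share the same risk. Seasonality is a supporting argument against calendar person-time, and the conclusion does not depend on it.

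**What to change.** Delete the person-time refinement from Section 7.2. State that both numerator and denominator are restricted to cohort members present at the ends of years K-1 and K who have a year-end stool result. This keeps the existing formula and makes explicit that those counted were examined.

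Counting infections measured at exit would also match the two parts, but it would need extra fieldwork and would leave the seasonal weighting of calendar time unresolved.

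A sensitivity analysis for drop-outs, using the age, sex, occupation, water-contact and baseline infection data already collected, is optional and can be left to the statistical analysis plan. The required change costs a few lines of protocol text and no new data collection.

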### 2.0 Study Objectives

This study aims to achieve the following objectives.

1. Repeat the results obtained from the TMRC-supported pilot intervention study, regarding the hypothesis that “Bovine, especially buffalo, infections are responsible for the persistence of human schistosomiasis transmission in the marshlands and lake areas of China.” However on a larger and more generalizable scale.
2. Examine the efficacy of bovine chemotherapy on human infection and reinfection rates and how this gives insight into the use of a potential bovine vaccine.
3. Assess bovine chemotherapy as a plausible schistosomiasis control method, particularly in combination with human treatment.
4. Integrate the empirical data collected from the study into the previously TMRC-developed mathematical model.
5. **Study Procedure**

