##### Outcome Measures

Humans:

Sentinel cohort members will receive 2 plastic containers for fecal samples. Containers will be labeled with PID, and the date of distribution. Participants will be instructed to deposit samples from their own faeces, separated by at most three days, into each container and to return the container immediately to one of several collection points, where the sample will be stored at 4 °C. Fecal samples returned later than 48 hours after defecation will not be accepted and new containers will be issued. Slide preparation (three slides per stool specimen) will occur 24 hours after receipt of stool sample using the Kato-Katz thick smear technique (Katz et al 1972). These samples will provide the outcome measures for each village 1 year after baseline. Water contact data will also be collected for that month via the completion of a questionnaire

Cohort members found to be egg positive will be treated for ethical reasons.

Water contact questionnaire survey

The questionnaire will be conducted once a year after transmission season (October-November) by trained team members, no more than 3 team members will be responsible for the survey for one village during the entire project period. The content of the water contact survey is listed in the questionnaire form. Each item must be answered with no blank.

Bovines:

A stool sample from every bovine will be collected and tested using the traditional Chinese MHT, These samples will provide the outcome measures for each village 1 year after baseline.

**Stage 5:** November 2005

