# Table of sample size (no new villages)

| Bovine effect size &  % Bovines treated | # Paired villages | Target sample size per village | Power %  (Year 1) | Power %  (Year 2) | Cumulative power  (Yrs 1 & 2) |
| --- | --- | --- | --- | --- | --- |
| 60% & 70% | 4 | 300 | 26.7 | 80.3 | 89.5 |
| 60% & 80% | 4 | 300 | 38.1 | 88.7 | 95.7 |
| 60% & 90% | 4 | 300 | 51.3 | 94 | 98.5 |
|  |  |  |  |  |  |
| 70% & 70% | 4 | 300 | 38.2 | 90.1 | 96.2 |
| 70% & 80% | 4 | 300 | 53.3 | 95.5 | 98.9 |
| 70% & 90% | 4 | 300 | 68.6 | 98 | 99.8 |
|  |  |  |  |  |  |
| 80% & 70% | 4 | 300 | 50.9 | 95.7 | 98.9 |
| 80% & 80% | 4 | 300 | 68.0 | 98.4 | 99.8 |
| 80% & 90 % | 4 | 300 | 82.7 | 99.4 | 100 |

Target sample size per village corresponds to the number of villagers sampled (not necessarily all those exposed). Powers are based on adjusting the sample size per village for attrition and a design effect.

- 1. **Analysis Plan**

Initial descriptive statistics will be performed to examine an overall trend in the data. This will be followed by the calculation of the outcome measures. These outcome measures will then be compared across control and intervention villages in order to determine the efficacy of the intervention. The empirical data gathered in this study will be put into the previously developed mathematical model (Williams *et al* 2002) in order to validate its predictions. Microsoft Access will be used for Data Management and SAS will be used for Data Analysis.

1. **Ethics**

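### From the second follow-up (K=3) the re-infected and newly-infected rates are taken in groups the intervention has already shaped, so comparing them across arms is not a like-for-like test of efficacy

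*Protocol*

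**What the plan says.** Section 7.2 gives three incidence-type measures for K=2 to 5. The overall incidence formula uses everyone in the cohort at the end of years K and K-1. The other two split that group by infection status at the end of year K-1:

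- The re-infected rate is introduced as "Rate of reinfection: This measure examines the rate of infection in those infected at the end of" the preceding year, and its denominator adds the condition "and positive at end of year K-1".
- The newly-infected denominator is restricted to cohort members at the end of "years K and K-1, and negative at end of year K-1".

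Section 7.1 lists reinfection rates among the outcome measures, and objective 2 is to "Examine the efficacy of bovine chemotherapy on human infection and reinfection rates". The Analysis Plan in section 7 states: "These outcome measures will then be compared across control and intervention villages in order to determine the efficacy of the intervention". Section 7.1 names human infection rates as the end-point and says: "Human infection rates will be assessed at the end of each year for 4 years".

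The protocol has no strata fixed at baseline and no caveat on reading the K-1 strata across arms.

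**The concern.** Randomization makes the two arms comparable as whole cohorts, and also within groups defined before the intervention can act. It does not make them comparable within groups defined by something the intervention changes. Infection status at the end of a year in which bovines were treated in one arm only is such a variable.

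If bovine treatment works, fewer intervention residents are positive at K-1, and they may differ in exposure from the control residents who are positive. The negatives may differ too. A difference between arms at year K then mixes the effect of treatment with a difference in who is being compared. At stake is the answer to the reinfection part of objective 2.

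**Working it through.** **1. Which years are affected.** There are four annual follow-ups and K runs from 2 to 5, so the end of year 1 is the October 2004 baseline. Bovine mass treatment begins in November 2004 (Stage 2). The October-November 2005 samples are the first outcome: "These samples will provide the outcome measures for each village 1 year after baseline".

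| K | Follow-up | Status used for the strata | Able to reflect bovine treatment? |
|---|---|---|---|
| 2 | Oct-Nov 2005 | Oct 2004 baseline | No |
| 3 | Oct-Nov 2006 | 2005 outcome | Yes |
| 4 | 2007 | 2006 outcome | Yes |
| 5 | 2008 | 2007 outcome | Yes |

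**2. How far the strata can diverge.** From the documents: 4 pairs x 300 = 1200 per arm; 20% attrition leaves 960; human prevalence is 10-15%. The power table's factors give reductions from 60% x 70% = 42% to 80% x 90% = 72% (multiplying the two factors is my reading). With the exposure models in step 3, the K-1-positive stratum at K=3 holds about 96-144 control members (960 x 0.10 to 0.15) and about 29-97 intervention members.

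**3. Size at K=3.** The protocol states no figure to reproduce. I read each numerator as restricted to its stratum, as the wording of 7.2 intends. Assumptions not in the documents: the spread of exposure, the effect by exposure group, independence between years given a person's exposure, and baseline risk equal to control annual risk.

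For exposure groups with weights w, control risks c and intervention risks t:

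- incidence ratio = Σwt / Σwc
- re-infected ratio (K-1 strata) = (Σwt²/Σwt) / (Σwc²/Σwc)
- ratio in the baseline-positive stratum = Σwct / Σwc²

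*A. Proportional effect, modest spread.* Exposure is gamma with mean 1 and variance 1, control risk 10%, reduction 42%. P(negative once) = 1/(1+r), so r = 0.1111 in control and 0.58 x 0.1111 = 0.0644 in intervention.
- Incidence: 0.1000 and 0.0605, ratio 0.61.
- Positive in both years: 1 - 2(0.9000) + 1/1.2222 = 0.01818, and 1 - 2(0.93946) + 1/1.1289 = 0.00691.
- Re-infected: 0.1818 and 0.1142, ratio 0.63. Newly-infected ratio: 0.63.
- Baseline-positive: (1 - 0.9000 - 0.93946 + 1/1.17556)/0.01818 = 0.62.

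*B. Effect mainly in low-exposure residents.* 20% have exposure 3.5 and 80% have 0.375; control risk 10% overall; reductions 20% (high) and 72% (low). With risk = 1 - exp(-r x exposure) and r = 0.115, c = 0.3312 and 0.0422, t = 0.2752 and 0.0120.
- Incidence ratio: 0.0646/0.1000 = 0.65.
- Re-infected: 0.02337/0.1000 = 0.2337 and 0.01526/0.0646 = 0.2361, ratio 1.01.
- Baseline-positive: 0.01864/0.02337 = 0.80.

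*C. Same direction, stronger contrast.* 10% have control risk 50% (risk ratio 0.9) and 90% have 8% (risk ratio 0.3), so t = 0.45 and 0.024.
- Incidence: 0.122 and 0.0666, ratio 0.55.
- Re-infected: 0.03076/0.122 = 25.2% and 0.02077/0.0666 = 31.2%, ratio 1.24.
- Baseline-positive: 0.02423/0.03076 = 0.79.
- With risk ratios 0.8 and 0.4 instead, the three ratios are 0.56, 0.98 and 0.73.

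*D. Effect mainly in high-exposure residents.* As B, with reductions 72% (high) and 20% (low): t = 0.1065 and 0.0339.
- Incidence ratio: 0.0484/0.1000 = 0.48.
- Re-infected: 0.00319/0.0484 = 0.0659 against 0.2337, ratio 0.28.
- Baseline-positive: 0.00820/0.02337 = 0.35.

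| Scenario | Incidence | Baseline-positive | Re-infected (K-1) |
|---|---|---|---|
| A | 0.61 | 0.62 | 0.63 |
| B | 0.65 | 0.80 | 1.01 |
| C | 0.55 | 0.79 | 1.24 |
| D | 0.48 | 0.35 | 0.28 |

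The step from incidence to baseline-positive is a real subgroup difference, since the effect truly differs by exposure and the same kind of people are compared in both arms. The step from baseline-positive to re-infected is the selection problem.

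**4. Check with no effect in the second year.** A fair comparison gives 1.00. With a first-year effect only, the K-1 strata give 1.02-1.11 (re-infected) and 1.04-1.37 (newly-infected) under a proportional effect, for gamma variance 1 or 4, risk 10% or 15% and reduction 42% or 72%. With unequal effects in two exposure groups, the re-infected ratio runs from 0.53 to 1.35.

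**The case against.** The intervention acts on bovines and so on the whole village, which makes a roughly proportional fall in risk as natural as an uneven one. In scenario A the distortion is negligible. Even the strongest proportional case examined (variance 4, 15%, 72%) gives 0.37 for incidence, 0.48 for re-infected and 0.49 for newly-infected, all clear benefit. This stands: apparent harm needs a markedly uneven effect, and nothing in the documents establishes one.

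The headline ratio would also be imprecise. In scenario C the K=3 strata hold about 960 x 0.0666 = 64 and 960 x 0.122 = 117 people. The standard error of the log ratio is √(0.688/(0.312 x 64) + 0.748/(0.252 x 117)) = 0.245, so 1.24 has a 95% interval of about 0.77 to 2.0, wider with the design effect of 1.5. If the trial stops at the two-year interim, only K=3 is affected. Both points stand, but imprecision does not restore comparability.

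Status at K-1 is a coherent definition of annual reinfection, and baseline strata ask a different question. Someone negative in 2004 and infected in both 2005 and 2006 is re-infected yet baseline-negative. This stands too, and is why the K-1 rates should be kept as description. The method for comparing secondary measures could be left to an analysis plan, but here the protocol itself fixes the strata and the use of the contrast as evidence of efficacy.

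A reader might infer that the main efficacy result is compromised because later years are accumulated with the first. The documents do not support that: 7.1 applies the accumulated comparison to human infection rates, and nothing says re-infection rates are accumulated. A reader might also infer that those still positive in intervention villages are the people bovine treatment failed to reach, so that the bias always hides benefit. That is an assumption, and scenario D runs the other way.

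**Conclusion.** The point holds for two secondary measures. For K=3 to 5, comparing the re-infected and newly-infected rates across arms as evidence of efficacy does not compare like with like. K=2, the end-point and the overall incidence formula are free of the problem, and the K-1 rates remain valid descriptions within each arm.

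The loss of comparability follows from the definitions alone. Its size and direction do not: they rest on exposure spread and effect variation that the documents do not give. It may be close to zero for re-infection, hide a real benefit or suggest harm, or exaggerate benefit. This is a worthwhile, inexpensive correction and does not threaten the trial's main result.

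**What to change.** In 7.2 and the Analysis Plan, state that the between-arm efficacy comparison in every year uses (a) unstratified incidence and (b) strata fixed by October 2004 infection status, labelled baseline-positive and baseline-negative rather than re-infected and newly-infected. State that the K-1 re-infected and newly-infected rates are within-arm descriptive figures and are not evidence of efficacy for K=3 to 5.

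The cost is wording and a regrouping of data already collected, since baseline status is recorded under an identifier kept throughout the study. The small downside is that baseline-positive is not the same as re-infected in later years, so both tabulations are needed.
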